## Abstract

**Background:**

To achieve the World Health Organization hepatitis C virus (HCV) elimination targets, it is essential to increase access to treatment. Direct-acting antiviral (DAA) treatment can be provided in primary healthcare services (PHCS), improving accessibility, and, potentially, retention in care. Here, we describe our protocol for assessing the effectiveness of providing DAAs in PHCS, and the impact on the HCV care cascade. In addition, we reflect on the challenges of conducting a model of care study during a period of unprecedented change in HCV care and treatment.

**Methods:**

Consenting patients with HCV infection attending 13 PHCS in Australia or New Zealand are randomized to receive DAA treatment at the local tertiary institution (standard care arm), or their PHCS (intervention arm). The primary endpoint is the proportion commenced on DAAs and cured. Treatment providers at the PHCS include: hepatology nurses, primary care practitioners, or, in two sites, a specialist physician. All PHCS offer opioid substitution therapy.

**Discussion:**

The Prime Study is the first real-world, randomized, model of care study exploring the impact of community provision of DAA therapy on HCV-treatment uptake and cure. Although the study has faced challenges unique to this period of time characterized by changing treatment and service delivery, the data gained will be of critical importance in shaping health service policy that enables the elimination of HCV.

**Trial registration:**

ClinicalTrials.gov, ID: NCT02555475. Registered on 15 September 2015.

**Electronic supplementary material:**

The online version of this article (10.1186/s13063-018-2768-3) contains supplementary material, which is available to authorized users.

## Background

Globally, approximately 71 million people have hepatitis C virus (HCV) infection, and each year 700,000 people die from HCV-related liver disease [1, 2]. The most common mode of HCV transmission in developed countries and increasingly in developing countries, is shared use of injecting equipment by people who inject drugs (PWID) and, therefore, the burden of disease is borne by current or former PWID [3]. Until 2014, the HCV care cascade demonstrated that few people completed diagnostic tests and received treatment [4, 5]. Treatment was only available from specialists in tertiary hospitals, where the need for a referral, inflexible appointment scheduling and lack of multidisciplinary care functioned as a barrier. Further barriers included: the toxicity and variable efficacy of pegylated interferon (PEG)-based therapy, the stigma experienced in healthcare settings and, historically, the need for a liver biopsy [6].

In the era of PEG-based therapy for HCV, many novel models of care were piloted in an attempt to increase the number of people commencing treatment. Strategies included: diversification of care providers to include specialist nurses, or primary care practitioners who had undertaken special training, expanding modes of interaction beyond face-to-face to include telephone or videoconference-based appointments, and offering care outside of tertiary hospitals in venues such as community drug and alcohol services and prisons [7–10]. The impact of these programs was curtailed by PEG-associated toxicity and the limited efficacy of PEG-based therapy.

The discovery of highly efficacious, well-tolerated direct-acting antiviral (DAA) therapy for HCV has revolutionized the treatment landscape, and has allowed innovative models of care to develop in order to improve the HCV care cascade. Globally, multiple treatment models have been implemented and evaluated in response to local DAA funding and prescribing requirements [11–13]. In Australia, since 1 March 2016 and in New Zealand since 1 October 2016, all primary care practitioners have been encouraged to prescribe DAAs, in consultation with a specialist physician if required [14]. All models are attempting to increase the number of people that are treated and cured, especially in priority populations such as PWID, in order to reduce incidence [15]. Given that treatment access policies around the world are currently highly divergent, it is important to obtain data to determine which models of care are most effective and cost-effective at increasing treatment uptake, with the ultimate aims of reducing transmission and preventing morbidity and mortality from HCV.

Some observational studies have reported improvements in retention in care and treatment uptake with the provision of multidisciplinary care to people who have chronic HCV [13, 16]. Further observational data supports HCV care and treatment in the community, usually in a facility with which the patient is already engaged [8, 10, 12, 17]. One small, randomized study of 21 patients suggested that treatment uptake of directly observed PEG therapy was higher in a community treatment center when compared to a tertiary hospital [18]. There is no study that directly compares the difference in retention in care, uptake of DAA treatment and cure outcome, if care and treatment is provided in the community, compared to at a tertiary hospital service. To investigate the effect of community-based HCV treatment on the care cascade, we have designed the Prime Study – to determine the impact of providing DAA treatment in the community on treatment uptake, and to directly compare tertiary hospital and community cure outcomes.

## Methods

### Study design

The Prime Study is an open-label, non-blinded, randomized controlled, effectiveness and implementation study. We initially aimed to recruit and randomly allocate 380 participants. We selected an effectiveness study design to enable comparison of the impact of community treatment on DAA treatment uptake across the two study arms, and simultaneously a non-inferiority study design to assess the effectiveness of community-based DAA treatment relative to an historical control group of people treated with PEG-based therapy. This study’s hybrid design combines testing effects of a clinical intervention on relevant outcomes whilst observing and gathering information on implementation [19]. The study protocol (version 7, 23 February 2017) follows the Standard Protocol Items: Recommendations for Interventional Trials (SPIRIT) Statement, see Additional file 1 (http://www.spirit-statement.org/). This trial has been registered at ClinicalTrials.gov (ID: NCT02555475).

### Study objectives

The primary objective of the study is:To estimate the proportion of people with HCV attending a primary healthcare service (PHCS) who commence DAA treatment at the PHCS and are cured; as measured by sustained virologic response rates 12 weeks post treatment (SVR12)

Secondary objectives are:2.To estimate the difference in the proportion of people with HCV infection attending a PHCS *who commence DAA treatment* if they are managed at their PHCS, compared to those who are referred to and managed at a tertiary hospital3.To estimate the difference in the proportion of people with HCV infection attending a PHCS *who obtain an SVR12* if they are managed at their PHCS, compared to those who are referred to, and managed at, a tertiary hospital4.To define the cascade of care for patients referred to a community hepatitis nurse for assessment of HCV5.To estimate the reduction in HCV prevalence and corresponding epidemiological impact if service delivery through PHCS was scaled up nationally6.To estimate the cost-effectiveness of managing and treating people in a PHCS compared to a tertiary hospital

### Study setting

This study is being conducted in Australia (Melbourne and Geelong) and New Zealand (Auckland and Christchurch). Community hepatitis nurses are employed by tertiary hospitals to work in PHCS in the community, providing an outreach service. All PHCS that the community hepatitis nurses attend provide opioid substitution therapy (OST), and many provide a variety of other services, i.e., needle and syringe distribution, and drug and alcohol counseling. In November 2015, eight PHCS affiliated with three tertiary hospital services in Victoria began recruitment. The Australian pharmaceutical benefits scheme (PBS) listing of DAAs on 1 March 2016 created a significant barrier for recruitment; therefore, the study was expanded, and a further five PHCS affiliated with two tertiary hospital services in New Zealand commenced recruitment in February 2017. The New Zealand Government has funded DAAs for people with a MELD < 15 only for genotype (Gt) 1 HCV, and, therefore, recruitment in New Zealand was limited to patients with Gt 1 infection.

### Study intervention

After consent has been obtained (see patient informed consent form, Additional file 2), the community hepatitis nurse performs initial screening and participants are randomized into one of two arms, as outlined below (see Fig. 1).

**Fig. 1 Fig1:**
[figure not shown]
Screening process, eligibility and randomization in the Australian and Auckland sites (**a**) and the Christchurch site (**b**)

#### Group 1 (standard tertiary care arm)

Participants with chronic HCV infection are referred for 12 weeks of DAAs treatment under the care of specialist physicians (gastroenterologists, hepatologists and infectious diseases physicians) at the local tertiary hospital

#### Group 2 (intervention PHCS arm)

Participants with chronic HCV infection receive 12 weeks of DAA treatment under the care of nursing and medical staff at their PHCS

### Randomization

Although patients are randomized at the end of the screening visit, a unique feature of this study is that randomization occurs before all screening procedures are complete. This is because pre-treatment assessment, which consists of blood tests and transient elastography (TE) (FibroScan**®,** Echosens), is a key part of the care cascade, and given that TE is not readily available in Australia or Auckland, in these study sites the location of TE is determined by the randomization result (see Fig. 1a). In Christchurch, TE is readily available in the community, and participants undergo TE at their PHCS as part of the screening visit (see Fig. 1b).

Participants are randomized to the two study arms using a block randomization approach. Randomization occurs at the PHCS level, to ensure equal numbers of patients from each PHCS are randomized to each arm. Random sequences of permuted blocks are generated, with each block allocating six study participants in a balanced fashion across treatment groups. Randomization is programmed using Stata version 13.0 and provided to study staff in sealed envelopes (Australian sites) or via REDCap database (New Zealand sites).

After the pre-treatment assessment has been completed, the results are reviewed in a follow-up appointment located at the tertiary hospital for group 1, and the PHCS for group 2. Eligible patients are then able to commence DAA treatment.

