### Eligibility and recruitment

#### Recruitment

Recruitment is undertaken by the community hepatitis nurses at each study site.

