### Sample size and power considerations

We designed a non-inferiority study to examine SVR12 outcomes of people treated in a PHCS, and to estimate the effect of providing DAA treatment in PHCS on treatment uptake using intention-to-treat analysis. Prior to the introduction of PEG-free therapy, approximately 10% of people with HCV who attended a PHCS commenced HCV treatment. Of those people, 70% completed therapy, which had an SVR12 rate of 85% [20]. We estimated that the number of people who commenced HCV treatment would substantially increase with DAA therapy to approximately 50% for people managed at PHCS, and 30% for people that attend tertiary hospitals. We attributed most of this difference to loss to follow-up after referral from the PHCS to the tertiary hospital, but before tertiary hospital attendance. We anticipated that 90% would be cured, regardless of whether they are treated at a PHCS or tertiary hospital, and that participants would have high levels of adherence [21].

Based on data from other community cohorts, we estimated 20% of participants would have screening TE results greater than 9.5 kPa, and would be excluded after being randomized. Given these response parameters and equal allocation across study groups, we estimated that 190 study participants were required in each arm in order to address the primary aim of the study and provide sufficient power for secondary aims.

*Aim 1: To determine if SVR12 outcomes of people treated in a PHCS are non-inferior to SVR12 achieved by historic controls.*

In keeping with initial DAA trials, our intervention arm was compared to historical controls [22, 23]. We hypothesized that the rate of SVR12 in people receiving DAA treatment in a PHCS would be non-inferior when compared to an SVR12 rate of 85% for historic controls treated with PEG, ribavirin and simeprevir. A sample of 76 (50% of 152) participants commencing DAA treatment at the PHCS would give a minimum of 90% power to show non-inferiority in those receiving DAA therapy using a 10% margin and an expected SVR12 response of 90% (one-sided α of 2.5%).

*Aim 2: To measure the difference in the proportion of people with HCV infection attending a PHCS who commence DAA treatment, if they are managed at their PHCS, compared to those who are referred to and managed at a tertiary hospital.*

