### Statistical analyses

For the primary aim (aim 1), an exact one-sided binomial hypothesis test will be undertaken to determine non-inferiority of DAA treatment in PHCS in terms of SVR12 response. For study aims 2 and 3, given the individual-level randomized nature of the design, Pearson chi-square tests [26] of independence will be undertaken in comparing differences in DAA therapy initiation and SVR12 across the two study groups. Statistical analyses will be performed using Stata version 13.0 [27].

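### A fixed block size of six within each primary care site leaves about a quarter of allocations deducible by an informed recruiter in this open-label trial

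*Protocol article*

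**What the plan says.** All references are to the protocol article.

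- **Block size (Randomization).** Permuted blocks are used, "with each block allocating six study participants in a balanced fashion across treatment groups". No second size and no random variation of size is mentioned.
- **Stratification (Randomization).** "Randomization occurs at the PHCS level, to ensure equal numbers of patients from each PHCS are randomized to each arm". This means a separate sequence per PHCS, not cluster randomization: Statistical analyses justifies its tests "given the individual-level randomized nature of the design".
- **Ratio (Sample size and power considerations).** The calculation starts "Given these response parameters and equal allocation across study groups", so a block holds three places per arm.
- **Blinding (Study design).** "The Prime Study is an open-label, non-blinded, randomized controlled, effectiveness and implementation study".
- **Who recruits (Recruitment).** "Recruitment is undertaken by the community hepatitis nurses at each study site". Study intervention gives the same role the initial screening, after which the participant is randomized.
- **Where the recruiters work (Study setting).** "Community hepatitis nurses are employed by tertiary hospitals to work in PHCS in the community, providing an outreach service".
- **Delivery of the sequence (Randomization).** Sealed envelopes in Australia, REDCap in New Zealand.

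**The concern.** Envelopes and REDCap hide the next assignment, but they do not stop anyone from working it out from earlier ones. Several features make that feasible here. Each PHCS has its own short sequence, and the only stated block size is six. Past allocations are also visible in daily work: the arm decides where follow-up takes place and, in Australia and Auckland, where transient elastography (TE) is done. In Australia the nurse may also deliver medication to participants in the PHCS arm.

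The between-arm outcomes are sensitive to who is enrolled into which place. Aim 2 counts people who start treatment and Aim 3 counts people who achieve SVR12. The sample size section attributes most of the expected difference between arms to loss to follow-up after referral. Engagement with care is plausibly something a nurse can judge before offering enrolment. If enrolment were timed so that more engaged patients fell into known places in one arm, the difference between arms would be biased, and the planned chi-square tests would neither detect nor correct it.

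**Working it through.** **Benchmark from the plan.** The article gives no predictability figure, so the yardstick is its detectable differences. With 190 × (1 − 0.20) = 152 per arm, 30% against 46% (Aim 2) gives 82.3% power, and 27% against 42.3% (Aim 3) gives 80.3%. Both agree with the stated 80% for 16 and 15.3 points.

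**Step 1: certain allocations in a complete block.** A 1:1 block of six has C(6,3) = 20 equally likely orders. An allocation is certain once one arm's three places are used.

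| Position | 1 | 2 | 3 | 4 | 5 | 6 |
|---|---|---|---|---|---|---|
| Probability already determined | 0 | 0 | 0 | 2/20 = 0.10 | 8/20 = 0.40 | 1.00 |
| Probability best guess is right | 0.50 | 0.60 | 0.60 | 0.70 | 0.70 | 1.00 |

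- Certain: 0.10 + 0.40 + 1.00 = 1.5 of 6 = 25%. The closed form for block size 2b is a share of 1/(b + 1); b = 3 gives 1/4.
- Best guess: the second row sums to 4.1, and 4.1/6 = 68.3%, against 50% by chance.
- The 25% is an average. One place is certain in 60% of blocks, two in 30% and three in 10%.

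**Step 2: incomplete last blocks.** Assume that 380 participants are spread evenly over 13 PHCS: ten sites with 29 and three with 30.

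- Site of 29: four complete blocks plus five places = 4 × 1.5 + 0.5 = 6.5.
- Site of 30: 5 × 1.5 = 7.5.
- Total: 10 × 6.5 + 3 × 7.5 = 87.5, and 87.5/380 = 23.0%.

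Smaller sites that stop partway through a block give less: 1.6/10 = 16%, 3/15 = 20% and 4.5/20 = 22.5%.

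**Step 3: possible bias in Aim 2.** Let s be the fraction of certain places that are steered, all in the same direction. Let d be the difference in propensity to start between patients put into certain PHCS places and those put into certain tertiary places. Bias = 0.25 × s × d. Both s and d are assumptions; the documents give neither.

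| | d = 10 points | d = 20 points |
|---|---|---|
| s = 50% | 1.25 | 2.5 |
| s = 100% | 2.5 | 5.0 |

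Against 16 points this is 1.25/16 = 8% to 5/16 = 31%. With the 23% share from step 2 the range is about 1.15 to 4.6 points. The formula counts only certain places. Steering on places that are merely likely would add to it.

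**Step 4: effect of varying the block size.** Simulation of 20,000 sequences of 30, with an observer who knows the set of sizes but not their order:

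| Scheme | Certain allocations | Best guess right |
|---|---|---|
| Fixed 6 | 25.0% | 68.3% |
| 4 and 6 | 5.7% | 68.8% |
| 4, 6 and 8 | 2.3% | 67.5% |

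Varying sizes removes certainty but hardly touches partial predictability.

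**The case against.** The strongest reply is that the key links are not documented. The article does not say that recruiting nurses know the block size, and printing it in a methods paper does not show that sites were told. That nurses keep track of earlier allocations, or judge motivation before consent, is plausible but inferred. The article also condenses a full protocol (version 7) that is not shown, and concealment from sites may be handled there. This stands, and it makes the point conditional. It does not remove the stated choice of one block size, which can also be inferred by watching a sequence that balances every six.

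A reader might infer that nurses would favour the PHCS arm because they work there. The documents do not support this: the nurses are employed by the tertiary hospitals, and no preference for either arm is shown. Steering could go either way or cancel between nurses.

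A reader might also take 5 points as the expected bias. It is the upper corner of the range, where every certain place is recognised, a suitable patient is at hand each time, and all steering favours one arm. Recruitment was hampered after DAAs were listed in Australia, which suggests little room to hold patients back.

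Finally, results were due in mid 2018, and SVR12 needs 12 weeks of treatment plus 12 of follow-up, so few allocations may remain to be changed.

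**Conclusion.** The design has an avoidable vulnerability. Over complete blocks of six, an observer who knows or infers the block size and follows one site's allocations could deduce 25% of them on average, or about 23% at the planned size if sites recruit evenly. It is too strong to say that the design makes a quarter of allocations certain in advance: that holds only for such an observer, and nothing shows that the nurses are in that position.

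The exposure is to the between-arm comparisons, Aims 2 and 3. Aim 1 compares people treated at the PHCS with a historical rate and is touched only through who enters that arm. Under the assumed 50% to 100% steering and 10 to 20 point difference in propensity, bias in Aim 2 would be about 1.25 to 5 points, against a detectable difference of 16. There is no evidence that any selection took place. The change is worth making because it is cheap.

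**What to change.** - **Remaining allocations.** Generate new lists with randomly varying block sizes (for example 4, 6 and 8) and do not disclose the sizes to sites. Issue them through REDCap at the Australian sites as well, releasing each allocation only after consent and the screening visit are logged. Full eligibility cannot be the trigger, because in Australia and Auckland TE is part of eligibility and follows randomization.
- **Participants already randomized.** Compare baseline covariates, which are collected at screening, by arm and position within block, in everyone randomized. Report the fixed block size as a limitation. Motivation itself is not among the listed data, so a clean comparison would reassure but not exclude selection.

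The cost is regenerating the lists and loading them into a system already in use. The downside is slightly larger possible imbalance within small PHCS. The benefit should be stated as it is: certain allocations fall to about 2%, while best-guess accuracy stays near 68%.

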### Study medications, dosage and administration

The medications being used for this study require a 12-week course of oral therapy.

Participants with genotype 1 are commenced on: paritaprevir 75 mg /ritonavir 50 mg/ombitasvir 12.5 mg co-formulated in one tablet, two tablets in the morning with food and dasabuvir 250 mg one tablet twice daily with food. For genotype 1a weight-based ribavirin was added: ≤ 75 kg 1000 mg daily in two divided doses or ≥ 75 kg 1200 mg daily in two divided doses.

Participants with genotype 3 are commenced on: sofosbuvir 400 mg one tablet daily and daclatasvir 60 mg one tablet orally daily.

Participants with genotype 4 are commenced on: paritaprevir 75 mg /ritonavir 50 mg ombitasvir 12.5 mg co-formulated in one tablet, two tablets in the morning with food and weight-based ribavirin as above.

In Australia, treatment medication is dispensed according to the randomization group. Participants randomized to group 1 fill their scripts at the tertiary hospital pharmacy. Participants randomized to group 2 fill their scripts at a community pharmacy, or have their medications delivered to their PHCS by their community hepatitis nurse. In New Zealand, treatment medication is dispensed according to local practice, which includes some tertiary hospital prescriptions being dispensed from community pharmacies. Participants self-administer the combination therapy.

